### **8.2.1 Reporting of serious adverse events**

For any SAEs occurring during study phase, investigators can carry out rescue and put on records according to each hospital’s standard operation procedure (SOP) on first aid emergencies. Investigator should report to the sponsor, AstraZeneca Patient Safety Department, Ethics Committee (EC), as well as provincial or municipal drug regulatory agency and China Food and Drug Administration (CFDA) within 24 hours since he/she is aware of it.

Investigators must be responsible for the follow-up of subjects with SAEs regularly. Follow-up reports about SAEs should be reported to the sponsor, AstraZeneca Patient Safety Department and EC within 24 hours.

### 8.3 Causality assessment of (severe) adverse events

The Investigator will assess causal relationship between investigational product and each AE/SAE, as well as the possible association with concomitant medicine using the following 5-level criteria:

**Definite:** It follows a reasonable temporal sequence from drug administration; it follows a known response pattern to suspected drug; it disappears on cessation of the suspected drug; it can't be caused by the subject's clinical state or other reasons.

**Probably:** It follows a reasonable temporal sequence from drug administration; it follows a known response pattern to suspected drug; it is obviously alleviated on cessation of the suspected drug; it can't be caused by the subject's clinical state or other reasons.

**Possibly:** It follows a reasonable temporal sequence from drug administration; it follows a known response pattern to suspected drug; it may be alleviated on cessation of the suspected drug; it may have been caused by the subject's clinical state or other reasons.

**Unlikely:** It may not follow reasonable temporal sequence from drug administration; it may not follow a known response pattern to suspected drug; it is not relieved on cessation of the suspected drug; it may have been produced by the subject's clinical state or other reasons and it may decrease when disease state improve or other reason removed.

**Unrelated:** It does not follow reasonable temporal sequence from drug

administration; It does not follow a known response pattern to suspected drug; It may readily have been caused by the subject's clinical state or other reasons and it may be relieved when disease state improve or other reason removed.

For SAEs, investigator will also assess causal relationship (with all medication/study procedures), and discussed with sponsor.

#### **8.4 Treatment on severe nausea and vomiting**

If the patient experience persistent or severe nausea and vomiting, investigators should look for possible causes. If there is clinical indication, serum creatinine should be measured, if serum creatinine rises sharply, metformin should be suspended until the recovery of renal function.

#### **8.5 Treatment on hypoglycemia**

Hypoglycemia includes asymptomatic and symptomatic hypoglycemia.

- Asymptomatic hypoglycemia: patient shows no discomfort, blood glucose < 3.9mmol/L. Carbohydrates should be taken to correct low blood sugar.
- Symptomatic hypoglycemia: experiencing sweating, palpitations, hunger, restlessness, anxiety, fatigue, irritability, headaches, difficulty in concentrating, lethargy, and visual disturbances, transient sensory or motor deficits, confusion, convulsions or coma, etc., monitoring of blood glucose level < 3.9mmol/L, or, above symptoms will immediately recover after administration of oral carbohydrates, intravenous glucose or glucagon even without obtaining blood glucose testing values,.
- Severe symptomatic hypoglycemia: acute neurological deficit directly caused by hypoglycemia events leads to the inability to self-treatment and the need of the assistance of others. The following characteristics will be shown: (1) blood sugar levels < 2.0mmol/L when experiencing the above symptoms; (2) without obtaining blood glucose level, but administration of oral carbohydrate, intravenous glucose or glucagon can immediately ameliorate symptoms.

Please note that "the need of the assistance of others" means the patient is unable of self-treatment. The situation that assistance is unnecessary, but only due to goodwill, does not meet the standard of "the need of the assistance of others".

When hypoglycemia meets the standards of serious adverse events, it should be reported as a serious adverse event. All convulsions, loss of consciousness or coma should be reported as a serious adverse event.

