| Safety Objective:                                                                                                                                                                                                                                                                                                                                                                                                                                                         | Outcome Measure:                                                                                                                                                                                                                                                                                                                                                                                                             |
| To assess the safety of saxagliptin (and vitamin D3) in LADA patients treated with metformin (and insulin).                                                                                                                                                                                                                                                                                                                                                                      | 
AEs/SAEs, especially severe hypoglycaemia and potential hypercalcemia;
 
Vital signs;
 
Collection of clinical/chemistry parameters;
 
ECGs.
                                                                                                                                                                                                                                                                  |

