### 2.3 Safety objectives and evaluating indicators

| Safety Objective:                                                                                                           | Safety Indicator:                                                                                                                                                     |
|-----------------------------------------------------------------------------------------------------------------------------|-----------------------------------------------------------------------------------------------------------------------------------------------------------------------|
| 
To assess the safety of saxagliptin with or without vitamin D3 in LADA patients treated with metformin (and insulin)
 | 
AEs/SAEs, especially Severe hypoglycaemia and potential hypercalcemia
 Vital signs
 Collection of clinical chemistry/haematology parameters
 ECGs.
 |

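### Read literally, section 8.5 puts an assisted hypoglycaemic event with a reading of 2.0 to below 3.9 mmol/L outside the severe class, but the same promptly recovering event with no reading inside it

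*Protocol*

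**What the plan says.** The synopsis objectives table names the safety outcome as "AEs/SAEs, especially severe hypoglycaemia and potential hypercalcemia", and section 2.3 repeats it. These are the only two events singled out among the AEs and SAEs.

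Section 8.5 supplies the definition. Asymptomatic and symptomatic hypoglycaemia both use a limit of 3.9 mmol/L. Symptomatic events may instead qualify without a reading if symptoms resolve at once after carbohydrate, intravenous glucose or glucagon. For the severe class the core condition is "acute neurological deficit directly caused by hypoglycemia events leads to the inability to self-treatment and the need of the assistance of others". The next sentence begins "The following characteristics will be shown" and lists two items:

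- The first is a measured value: "blood sugar levels < 2.0mmol/L when experiencing the above symptoms".
- The second covers events where nobody measured glucose: symptoms must ease at once when the patient is treated for low glucose.

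They are called characteristics (1) and (2) below. The section then explains what needing assistance means. It closes with a separate reporting rule: "All convulsions, loss of consciousness or coma should be reported as a serious adverse event".

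**The concern.** The core condition is functional: a deficit, and dependence on another person. The two listed characteristics add a glucose condition that applies only when someone has taken a reading. An assisted event measured between 2.0 and 3.9 mmol/L satisfies the core condition and is hypoglycaemia under section 8.5, yet it matches neither characteristic. Without the measurement, and with prompt recovery, it would have matched the second.

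At stake is the count of an outcome that the protocol itself picks out. Section 6.4.1 distributes glucose meters at Visit 1 and section 6.1 has every self-measured value entered in a diary, so readings in this range are a practical possibility. Sites classify events from this text as they occur. Two investigators facing the same episode could label it differently, or both could leave out an episode that meets the need-for-assistance sentence.

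**Working it through.** The protocol gives no figure to reproduce here; the check is of the definition.

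**Inputs, all from section 8.5.** Let g be the glucose reading in mmol/L, if one was taken, and R mean immediate improvement after treatment. Every event considered has the neurological deficit and the need for assistance.

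- Symptomatic: (reading taken and g < 3.9) or (no reading and R).
- Severe: core condition, plus (1) reading taken and g < 2.0, or (2) no reading and R.

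**How (1) and (2) combine.** Characteristic (1) needs a reading and (2) needs the absence of one. If both were required, no event could ever be severe, so they must be alternatives.

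**Applying the rules to one assisted event:**

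| Reading | Immediate improvement | Symptomatic | Severe |
|---|---|---|---|
| none | yes | yes | yes, by (2) |
| none | no | no | no |
| 1.5 or 1.9 | yes or no | yes | yes, by (1) |
| 2.0, 2.5, 3.0 or 3.8 | yes or no | yes | **no** |
| 3.9 | yes or no | no | no |

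Compare the first row with the fourth when improvement is immediate. The patient, the deficit, the help given and the recovery are the same; only the existence of the reading differs, and the class changes. The affected range is 2.0 to below 3.9 mmol/L. The second row shows that an unmeasured event does not count automatically, because immediate improvement is also required.

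**Are the characteristics conditions or description?** The symptomatic definition just above has the same two-part form (a reading below a limit, or recovery without a reading), and there the two parts are the definition. That makes the conditional reading the natural one for the severe class. If they are only description, the sentence still says that a severe event will show them, which is untrue of an assisted event at, say, 2.5 mmol/L. Either way the two sentences disagree over this range.

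**The case against.** The strongest reply is that need for assistance is the operative criterion. The text does not say an event must meet one of the two items, and the only term the section goes on to explain is assistance. On that view nothing is excluded. This is a fair reading and the reason the point is put as a literal one, but it leaves the inconsistency shown above and gives sites no instruction for this range.

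A second reply is that section 9.4.3 specifies no severe-hypoglycaemia count, and tabulation may be left to an analysis plan not shown here. That is correct as far as tables go. The definition, however, is fixed in the protocol, and sites apply it before any table is made.

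Four stronger conclusions are tempting, and the documents do not support them:

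- **That the events disappear from the safety data.** They do not. Section 8.1.1 records all AEs, section 8.1.2 grades intensity with no glucose condition, and the SAE criteria in 8.2 still apply. Only the severe label in 8.5 is at issue.
- **That the SAE line contradicts the definition.** A coma at 2.5 mmol/L would be an SAE but, read literally, not severe hypoglycaemia. Section 8.2 expressly separates serious from severe, so this is a difference of label, not a contradiction.
- **That a known share of events is missed.** The documents do not say how often assisted events have a reading, or how such readings are distributed. Distributing meters does not show that a patient unable to self-treat was measured.
- **That the arms are affected unequally.** The trial is open-label and insulin is adjusted at the investigator's discretion, but insulin is individualised in every arm and any difference in dose is a secondary outcome to be tested. Unequal misclassification is possible but not shown.

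**Conclusion.** The point holds as a defect of definition. Taken literally, section 8.5 excludes from the severe class any assisted event with a reading from 2.0 to below 3.9 mmol/L and includes the same promptly recovering event when no reading exists. The conclusion rests on treating the two characteristics as alternative conditions; if they are descriptive, the section is instead inconsistent over the same range and still needs one clarifying line.

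The size cannot be derived. In principle it runs from none of the assisted events to all of them, depending on how many have a reading in the range. Neither the primary analysis nor the capture of AEs and SAEs is affected. The point matters because this is one of two events that the protocol singles out for safety, and because the correction is simple.

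**What to change.** Reconcile the need-for-assistance sentence in section 8.5 with the two listed characteristics: state how an assisted event with a reading from 2.0 to below 3.9 mmol/L is classified.

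In the safety tables, report by arm all events meeting the protocol's own need-for-assistance criterion, with those showing characteristic (1) and those showing characteristic (2) as subsets. The CRF should record whether assistance was needed, whether a reading was taken and its value, and whether improvement was immediate, so that each event can be placed under either interpretation.

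This concerns classification and reporting only; it prefers no glucose threshold and changes no treatment. The cost is one line in 8.5 and the CRF, and a reported count that may be higher than under the literal rule.

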## 8.6 Treat on hypercalcemia

Clinical manifestations of hypercalcemia are associated with the magnitude and speed of the increase of serum calcium. Mild hypercalcemia may be asymptomatic. symptoms include anorexia, nausea, vomiting, constipation, fatigue, muscle fatigue, reduce of muscle tension, polydipsia, polyuria; drowsiness, confusion, and even coma. ECG may show shortening of Q-T interval, the change of ST-T, atrioventricular block and hypokalemic u waves. If not treated timely, it may result in fatal arrhythmia. Long duration of hypercalcemia can lead to calcium deposition within various tissue and organ, such as the conjunctiva, periarticular and kidney stones. It should be noted that serum albumin have impact on calcium concentration. Elevated serum calcium levels can be categorized into mild, moderate and severe.

- Mild hypercalcemia: total serum calcium values above the upper reference limit, but  $< 3\text{mmol/L}$ ;
- Moderate hypercalcemia: total serum calcium values  $3\text{-}3.5\text{mmol/L}$ ;
- Severe hypercalcemia: total serum calcium  $> 3.5\text{mmol/L}$ , while causing a series of serious clinical manifestations, namely hypercalcemia crisis.

The most common causes of hypercalcemia are primary hyperparathyroidism and malignant tumors, other reasons include: drugs: such as vitamin D, vitamin A, thiazide diuretics, lithium, theophylline, estrogen and anti-estrogen hormones; endocrine diseases, sarcoidosis and other granulomatous diseases, long-term immobilization, familial hypocalcinuric hypercalcemia and milk alkali syndrome. Once the patient's serum calcium is high:

- Confirm the existence of hypercalcemia, measure of serum calcium should be repeated to rule out laboratory error and prolonged tourniquet lashing or other human factors; be aware whether the patient is dehydrated or rise of plasma protein concentration.

- Once hypercalcemia is confirmed, the cause should be identified: researchers can determine whether to simultaneously monitor PTH, 25(OH)D, renal function, urinary calcium/creatinine clearance rate and alkaline phosphatase based on the patient's condition, and seek for other possible causes; if the patient is in the vitamin D3 treatment group, vitamin D3 therapy should be suspended.
- Treatment of hypercalcemia depends on calcium levels and clinical symptoms. In aspect of mild hypercalcemia, generally no active measures are taken to control blood calcium in patients without clinical symptoms; for symptomatic moderate and severe hypercalcemia patients, immediate treatment may be required according to the cause; when calcium > 3.5 mmol/L, regardless of the presence or absence of clinical symptoms, immediate and effective measures are required: dilatation, promote urinary calcium excretion, inhibit bone absorption, glucocorticoids, and even dialysis to lower blood calcium [26].

When the cause and manifestation of hypercalcemia meet the standards of serious adverse events, it should be reported as a serious adverse event.

## **8.7 Treatment on vitamin D intoxication**

Vitamin D intoxication has no particular manifestation, similar to hypercalcemia. Early phase of acute intoxication first presents with increased serum 25-OHD and calcium, change of epiphysis appearing later. Abnormal X-rays can assist diagnosis, but negative results cannot rule out the possibility of vitamin D intoxication.

In the “Application Guideline for Vitamin D and Bone Health in Adult Chinese”, it refers American guideline that it is considered as potential vitamin D intoxication if 25(OH)D > 500nmol/L (200ng/ml) continuously. However, the actual incidence of vitamin D intoxication is low and it happens rarely in accidental overdose or inappropriate treatment with large dose.

In this study, the daily dose of vitamin D should be reduced to 800IU, if 25(OH)D>250nmol/L. When serum 25(OH)D>500nmol/L (200ng/mL), study should be suspended, withdrawal vitamin D and calcium, avoid sunlight, apply low calcium diet. Adrenal hormones can inhibit the intestinal absorption of calcium, and antagonize VitD. its impact on blood glucose should be noted.

When vitamin D intoxication meets the standards of serious adverse event, it should be reported as serious adverse event.

## **8.8 Overdose**

An overdose (accidental or intentional) with the investigational drugs is an event suspected by the investigator or spontaneously notified by the patient and defined as at least twice of the intended dose within the intended therapeutic interval (e.g. within one calendar day)-. If an overdose on a AZ study drug occurs in the course of the study, then investigators or other site personnel inform sponsor immediately when he or she becomes aware of it.

An overdose with associated AEs should be recorded as the AE diagnosis/symptoms on the relevant AE modules in the CRF and also on the Overdose CRF module. An overdose without associated symptoms only needs to be reported on the Overdose CRF module.

## **8.9 Pregnancy**

Before signing the informed consent, investigators should notify childbearing age participants of the importance of contraception throughout the study and the potential risks of accidental pregnancy. The subject must sign the informed consent to claim that the investigator has discussed the risk factors and outcomes with her.

If a subject becomes pregnant during the course of the study, investigational product should be discontinued immediately and the procedure of study discontinuation of the subject should be finished. Pregnancy itself is not regarded as an adverse event unless there is a suspicion that the investigational product under study may have interfered with the effectiveness of a contraceptive medication. Congenital abnormalities/birth defects and spontaneous miscarriages should be reported and handled as SAEs. Elective abortions without complications should not be handled as AEs. The outcome of all pregnancies (spontaneous miscarriage, elective termination, ectopic pregnancy, normal birth or congenital abnormality) should be followed up and documented even even the subject was discontinued from the study.

If any pregnancy occurs in the course of the study, then investigators or other site personnel inform sponsor within one day.

The same timelines apply when outcome information is available.

## 9. STATISTICAL ANALYSIS

All data are analyzed by SAS 9.3 software (SAS Institute Inc.,Cary,NC,USA).

### 9.1 Statistical considerations

Statistical analysis will be performed by selected biostatistics professionals. A comprehensive Statistical Analysis Plan (SAP) will be prepared before database locked. Exploratory analysis is allowed to make changes to adapt to unexpected issues during the study.

### 9.2 Sample size estimation

The sample size calculations were performed based on the primary variable “absolute change in fasting C-peptide from baseline to 104-week”.

Because there is no study for the effect of Saxagliptin combined with vitamin D3 on  $\beta$ -cell function of diabetes patients, the sample size calculations in this study is based on early published literature comparing the effect of sitagliptin combining insulin and insulin therapy alone on  $\beta$ -cell function in LADA patients with the course of diabetes less than 1 year. Our study hypothesis is that saxagliptin will improve the protective effect on  $\beta$ -cell function in LADA treated with metformin (and insulin) than those with metformin (and insulin) alone, and saxagliptin combined with vitamin D will also further improve protective effect on  $\beta$  cell function in LADA treated with metformin (and insulin) than those with metformin (and insulin) alone. The means of effect of insulin treatment group and sitagliptin combining insulin group on fasting C-peptide (extent of fasting C-peptide changing from baseline to 1 year later ) which is the indication of  $\beta$ -cell function are 149.2, 108.4 individually, the standard deviations are 84.5, 52.8 individually. As twice test involved, set two-sided  $\alpha=0.025$  as significance level, and set  $\beta=0.1$  that means the power of test is 90%. According to the formula used to compare the means of two-sample:

$$n = 2 \left[ \frac{(\mu_{\alpha} + \mu_{\beta})}{\delta/\sigma} \right]^2 + \frac{1}{4} \mu_{\alpha}^2$$

Calculating with the formula and above values, we can get the sample size  $n=76$ .

According to calculation with the drop-out rate which is approximate 20%, 95 patients per group are needed. We set 100 cases per group, 300 cases in total.

### **9.3 Definitions of analysis sets**

The primary efficacy analysis population will be based on the Full Analysis Set (FAS) and the Per-Protocol Analysis Set (PP). The secondary analysis population and the safety analysis population will be based on the Per-Protocol Analysis Set (PP) and Safety Analysis Set (SS), respectively.

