### 3. STUDY DESIGN

This is a multi-center, open-label, 1:1:1 randomized controlled trial, involving 20-45 centers among the country, and a total of 300 subjects, and is a prospective research comprising of a 104-week open-label intervention period.

On the basis of the inclusion/exclusion, eligible patients will be selected to be randomly allocated into groups and initiate the 104-week open-label intervention period. A central randomization system will be adopted, and the study population will be stratified based on the following: fasting C-peptide (FCP)  $\geq 300$  pmol/L and  $< 300$  pmol/L; GADA titer  $\geq 0.3$  and  $< 0.3$  index; BMI  $\geq 25$  kg/m^2 and  $< 25$  kg/m^2. Patients will be randomized into the following three groups: metformin (and insulin), metformin (and insulin)+saxagliptin, metformin (and insulin)+saxagliptin+vitamin D3 (Figure 1).

[figure not shown]

Figure 1. Study Flow Chart

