## **5.5 Prohibition of drugs**

Other hypoglycaemic drugs, including sulfonylureas, glinides, alpha-glucosidase inhibitors, thiazolidinediones, GLP-1 agonists, and other DPP-IV inhibitors should not be used throughout the trial.

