##### **Full analysis set (FAS)**

The Full analysis set will include all randomized subjects, including those who took at least 1 dose after randomization, and had at least 1 baseline and post-baseline efficacy data assessments. Subjects on FAS will be analyzed by the treatment group they were randomized to. The Full analysis set will be the primary set for efficacy analysis in the study.

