##### **Per protocol (PP) analysis set**

The PP analysis set is a subset of the Full analysis set that includes subjects who do not have significant protocol deviations that affect the study outcome. These exclusions from the PP analysis set will include but not be limited to the patients who took prohibited concomitant medications and major protocol deviations or violations. The exclusions from the PP analysis set will be determined prior to database lock on data review meeting.

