### **9.4.1 Analysis of the primary variable(s)**

The primary endpoints in the study are absolute fasting C-peptide changes between saxagliptin + metformin (and insulin) group vs. metformin (and insulin) group, and vitamin D + saxagliptin + metformin (and insulin) group vs. metformin (and insulin) group from baseline after 104 weeks of treatment. The primary endpoint will be analyzed utilizing mixed model repeated measures (MMRM) on full analysis set (FAS). Within the framework of MMRM, point estimations and 2-sided 95% CIs will be presented at each visit for the mean change within each treatment group as well as the difference of the mean change between treatment groups. The following hypothesis will be tested to establish superiority:

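### Section 9.3 places the secondary analyses on the per-protocol set, against the protocol's own choice of the FAS for efficacy; the confirmatory primary test itself stays on the FAS

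*Protocol*

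**What the plan says.** Section 9.3 of the protocol assigns populations in two sentences. For the primary: "The primary efficacy analysis population will be based on the Full Analysis Set (FAS) and the Per-Protocol Analysis Set (PP"). For the rest: "The secondary analysis population and the safety analysis population will be based on the Per-Protocol Analysis Set (PP"), after which the sentence names the Safety Analysis Set and closes with *respectively*. With that word, secondary pairs with PP and safety with the Safety Analysis Set.

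Section 9.3.1 then says of the FAS: "The Full analysis set will be the primary set for efficacy analysis in the study". That statement is not limited to the primary endpoint. The intention-to-treat paragraph just before it argues for analysis by initial assignment, because this guards against distortion from non-random loss of subjects.

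Section 9.3.1 forms PP by removing, among others, "the patients who took prohibited concomitant medications and major protocol deviations or violations". The list is expressly open-ended and is settled at a data review meeting before database lock. Section 5.5 defines the prohibited drugs: "Other hypoglycaemic drugs, including sulfonylureas, glinides, alpha-glucosidase inhibitors" and further glucose-lowering classes.

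Section 9.4.1 runs the primary mixed model on the FAS and reports within-group changes and between-group differences at each visit. Section 9.4.2, on the secondary variables, names no analysis set.

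**The concern.** Section 3 describes a "multi-center, open-label, 1:1:1 randomized controlled trial", and section 9.4.1 states its aim: "The following hypothesis will be tested to establish superiority". In such a trial the comparison is protected by keeping subjects in the arm to which they were randomised. PP removes them for things that happen afterwards, while patient and investigator know the treatment. One named ground for removal, use of another glucose-lowering drug, may be related to the endpoints being compared, since HbA1c, HbA1c below 7% and insulin dose are all secondary endpoints in section 2.2.

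Removal may also be unequal by design. The notes to Table 1 say that Group A receives no investigational medication. If non-compliance with that medication (section 5.4) were counted as a major deviation, only the two active arms could lose subjects on that ground.

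At stake is whether the secondary comparisons, which the synopsis tests at 0.05, are comparisons of randomised groups. A second problem is that the sections do not agree on which set applies.

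**Working it through.** **Step 1. Set the sections side by side.**

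| Analysis | 9.3 | 9.3.1 / 9.3.2 | 9.4 |
|---|---|---|---|
| Fasting C-peptide, week 104 (primary) | FAS and PP, unranked | FAS | 9.4.1: FAS |
| Fasting C-peptide, weeks 26, 52, 78 (secondary) | PP | FAS | 9.4.1: FAS, differences at each visit |
| Other secondary endpoints in 2.2 | PP | FAS | 9.4.2: no set named |
| Safety | Safety set | Safety set | 9.4.3: no set named |

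Row 1: two of three places give the FAS alone, including the section that specifies the test. Row 2: one set of estimates is given two populations, and the specific section says FAS. Row 3: only the general wording of 9.3.1 opposes 9.3, so 9.3 is the only text that speaks of secondary analyses by name. This row holds meal-test C-peptide, the C-peptide response proportions, HbA1c and HbA1c below 7%, insulin dose, GADA, and weight and BMI. Row 4 is consistent.

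**Step 2. Can the size of any bias be derived?** No. The protocol gives no PP exclusion rate, no split by arm and no relation between exclusion and outcome. The two calculations below rest on assumptions and show a range only.

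*Shift in mean HbA1c.* Assume excluded subjects lie 1.5 points above their arm mean. Removing a fraction p lowers the arm mean by 1.5p/(1 − p).
- 10% of control, 4% of active: 0.15/0.90 = 0.167 and 0.06/0.96 = 0.063; the difference moves by 0.104.
- 20% and 5%: 0.30/0.80 = 0.375 and 0.075/0.95 = 0.079; the difference moves by 0.296.
- Equal fractions: no shift.

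Here control loses more high values, so the shift works against the active arm. With the fractions exchanged it works in favour.

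*False-positive rate.* Assume no true effect, 100 per arm, a two-sided 0.05 test, and exclusion in one arm only of the fraction f that is highest on a variable with correlation ρ to the endpoint. The spread of the trimmed arm is taken as unchanged. In SD units:
- shift = ρ·φ(z)/(1 − f), with z the upper-f normal point: 0.1755/0.9 = 0.195 times ρ for f = 0.10, and 0.280/0.8 = 0.350 times ρ for f = 0.20;
- SE = √(1/100 + 1/(100(1 − f))) = 0.145 and 0.150;
- error = Φ(shift/SE − 1.96) + Φ(−shift/SE − 1.96).

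| ρ | f | shift (SD) | error |
|---|---|---|---|
| 0 | 0.10 or 0.20 | 0 | 5.0% |
| 0.3 | 0.10 | 0.059 | 6.9% |
| 0.3 | 0.20 | 0.105 | 10.8% |
| 0.5 | 0.10 | 0.097 | 10.3% |
| 0.5 | 0.20 | 0.175 | 21.5% |

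The ratio shift/SE does not depend on the SD, so the table applies to any of the continuous endpoints.

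**Step 3. Does changing the set affect the planned size?** Section 9.2 gives means 149.2 and 108.4 (difference 40.8) and SDs 84.5 and 52.8, so σ = √((84.5² + 52.8²)/2) = 70.46. With two-sided α = 0.025 and 90% power, its formula gives 2[(2.241 + 1.282)/(40.8/70.46)]² + 2.241²/4 = 75.28, hence 76; 76/0.8 = 95, set to 100. The plan's figures reproduce. They concern the primary endpoint, and the choice of set for the secondary endpoints does not enter them.

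**The case against.** - *The primary is already settled.* Correct. A reader might infer from section 9.3 that the confirmatory test drops subjects for protocol deviations, or that nothing says which set decides. Sections 9.3.1 and 9.4.1 do not support that: the model and the superiority test are on the FAS. For the primary, what remains is an unranked second population in a summary sentence.
- *Not every secondary endpoint is affected.* Correct. A reader might infer that all of them fall to PP, or that one fasting C-peptide model would use two populations. Section 9.4.1 reports differences at each visit from the FAS model, so weeks 26, 52 and 78 are covered there. The conflict with 9.3 is a contradiction between sections, not a split model.
- *The term is ambiguous.* The phrase for the secondary population could mean a supporting population, with the FAS leading throughout. That would agree with section 9.3.1. The preceding sentence and the pairing with the safety set make a population for the secondary analyses the more natural reading, but if both readings are possible the text still needs repair.
- *Insulin is the planned response to worsening glycaemia.* This stands in part. Insulin is permitted in every arm and adjustable at the investigator's discretion (sections 1.3 and 5.2), and it is not on the list in 5.5. Outcome-related exclusion through prohibited drugs is therefore possible but not shown to be likely. The open-ended list leaves other routes.
- *Exclusions are fixed before lock.* This limits the risk. It does not remove it when treatment is known. Whether the meeting sees results is a detail that a statistical analysis plan may settle, so that silence is not counted here.

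**Conclusion.** The point holds in limited form. Section 9.3 puts the secondary analyses on PP and lists PP unranked beside the FAS for the primary, in conflict with sections 9.3.1 and 9.4.1 and with the protocol's own argument for analysis as randomised. For the secondary endpoints other than fasting C-peptide at weeks 26, 52 and 78, following 9.3 as written gives comparisons in which randomisation is not preserved.

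Neither size nor direction of any resulting bias can be derived from the documents. The 0.10 to 0.30 HbA1c points and the 5% to 21.5% error rates depend wholly on assumed exclusion rates and correlations; with equal exclusion in the arms the HbA1c shift is zero, and with exclusion unrelated to outcome the error stays at 5%. A reader who took these figures as a forecast for this trial, or took the shortened quotation as placing safety on PP, would go beyond the text.

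The confirmatory test, its 0.025 level and the sample size are untouched. This should be fixed, but it does not endanger the main conclusion.

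**What to change.** In section 9.3, state that all primary and secondary efficacy endpoints are analysed in the FAS by randomised arm; that the FAS alone decides the primary; and that PP is supportive only, with its exclusions fixed before lock by people who see neither allocation nor outcome results. Keep safety on the Safety Analysis Set. Name the FAS in section 9.4.2, and check that 9.3, 9.3.1, 9.4.1 and 9.4.2 then agree.

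The cost is a few sentences. The same programs run on a different set, no further data are collected, and 76, 95 and 100 per group stand. If the change were left to the statistical analysis plan announced in section 9.1, that plan would depart from the protocol's wording, so the protocol should be amended too.
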